#### 2.2.1. Primary Objective

An overall cumulative acute/subacute skin toxicity grade of ≥3 CTCAE (Common Terminology Criteria for Adverse Events), NCI (National Cancer Institute), version 5.0, associated with study treatment within 6 months after the start of re-RT.

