### 2.4. Statistical Considerations and Sample Size Calculation

The sample size calculation is based on a single-arm study on the primary endpoint, namely the overall occurrence of acute/subacute skin toxicity, CTCAE, of grade ≥ 3, assessed within the first 6 months after the start of the re-RT. The following one-sided null hypothesis is to be tested: $H_{0}:p_{Tox}\geq 25\%$ (i.e., a toxicity rate of 25% for photon re-RT [31] should not be exceeded). For the sample size calculation, a better toxicity rate of 3% [49,56] for proton re-RT was assumed. Based on these assumptions, a required number of 20 patients were calculated for a one-sided binomial test at the level α = 0.025 in order to achieve a power of 1 − β = 0.8, while a one-sided 97.5% confidence interval was calculated. Under these assumptions, the actual level is 0.0243, the actual power is 0.88, and the critical value is 1, i.e., the null hypothesis cannot be rejected if more than one patient experiences a grade ≥ 3 toxicity. The sample size calculation was carried out using the rpact package of the open-source software R (Version 3.0, RPACT; Cologne, Germany).

The populations for analysis include the Intention-to-Treat (ITT) population (all the enrolled patients who fulfilled the in-/exclusion criteria and have submitted their written informed consent and have been treated for at least 1 day) and the complete case population: all the patients in the ITT population who were able to receive the planned therapy in full and whose documentation is correspondingly complete. This is the primary evaluation population for primary and secondary endpoints.

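### The primary toxicity test is run on patients who completed therapy with complete documentation, so a patient who stops permanently because of grade ≥ 3 skin toxicity has the primary event but is left out of the test

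*Protocol article*

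**What the plan says.** Section 2.4 of the protocol article names two analysis sets. The set called ITT contains enrolled, eligible, consented patients treated for at least one day. The complete case set is "all the patients in the ITT population who were able to receive the planned therapy in full and whose documentation is correspondingly complete". The next sentence reads "This is the primary evaluation population for primary and secondary endpoints". It follows directly on the complete case definition and is singular, so it most naturally refers to that set.

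The endpoint is skin toxicity of CTCAE grade ≥ 3 "associated with study treatment within 6 months after the start of re-RT" (section 2.2.1). Section 2.4 repeats the window as running from the start of re-irradiation, so events during the 15 fractions count.

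On the design, section 2.4 says "a required number of 20 patients were calculated for a one-sided binomial test at the level α = 0.025", and reports that "the actual level is 0.0243, the actual power is 0.88, and the critical value is 1". Section 2.1 plans to include 20 patients, which equals the calculated number.

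Section 2.4 also rules out imputation of the primary endpoint. It promises a descriptive report of missing values, emphasis on the resulting limitations, and a tabulation of (serious) adverse events. It states no test of the primary endpoint in all treated patients.

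**The concern.** Membership of the primary set is decided after treatment starts and can depend on the outcome. Severe skin toxicity is a plausible reason for not completing radiotherapy. A patient who stops permanently for that reason has had exactly the event the trial counts, yet is not in the set in which it is counted. The documentation condition can likewise remove a patient whose event is already on record. When exclusion is linked to toxicity in this way, the error runs in one direction, towards declaring the rate below 25%.

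The decision rests on one versus two events in 20 patients, so very few exclusions matter. The article says the study will provide the basis for a randomized trial, and this test is its only confirmatory result.

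**Working it through.** **Inputs from section 2.4.** Null rate p0 = 0.25, assumed proton rate p1 = 0.03, n = 20, one-sided α = 0.025, H0 rejected if at most 1 event is seen.

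**Input not in the documents.** The share f of event patients who leave the complete case set. I take f = 0.1, 0.2, 0.3 and 0.5 as assumptions.

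**1. Reproduce the design.** P(X ≤ 1) = (1−p)^20 + 20·p·(1−p)^19.
- At p = 0.25: 0.0032 + 0.0211 = 0.0243, as stated.
- At p = 0.03: 0.5438 + 0.3364 = 0.880, as stated.

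The design arithmetic is correct for 20 analysed patients.

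**2. Exclude event patients only, true rate 25%.** The expected rate in the complete case set is p(1−f)/(1−pf). For f = 0.1 this is 0.225/0.975 = 23.1%. The probability of wrongly rejecting H0 depends on how the test is run on the reduced set:
- (a) Exact critical value re-derived for the remaining number, by enumeration over the number of events and the number excluded.
- (b) Excluded patients replaced until there are 20 complete cases: P(X ≤ 1) for a binomial with n = 20 and the rate in the second column.
- (c) Critical value of 1 kept regardless: remaining events are binomial with n = 20 and rate 0.25(1−f).

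| f | Expected rate | (a) exact, reduced n | (b) replaced to 20 | (c) critical value 1 kept |
|---|---|---|---|---|
| 0 | 25.0% | 0.024 | 0.024 | 0.024 |
| 0.1 | 23.1% | 0.025 | 0.037 | 0.042 |
| 0.2 | 21.1% | 0.028 | 0.056 | 0.069 |
| 0.3 | 18.9% | 0.036 | 0.085 | 0.112 |
| 0.5 | 14.3% | 0.079 | 0.199 | 0.267 |

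Column (a) is closest to the stated exact binomial test. Its first non-zero entry is 0.0251, essentially the nominal level.

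**3. Exclude some event-free patients too.** Suppose 5% of event-free patients also leave (an assumption). Under (a), false rejection becomes 0.013, 0.018, 0.027 and 0.072 for f = 0.1, 0.2, 0.3 and 0.5. At the two lower shares the level is below 0.025.

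**4. Power.** With 13 to 19 analysed patients the exact critical value is 0. At n = 19 the level is 0.75^19 = 0.0042 and the power is 0.97^19 = 0.561. With 5% of event-free patients lost and no event patients lost, power averages 0.67 instead of 0.88.

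**5. Worked cases.**
- 2 events in 20 treated: p = 0.091, H0 not rejected.
- One of the two excluded and replaced by an event-free completer: 1 in 20, p = 0.0243, H0 rejected.
- One excluded without replacement: 1 in 19, exact p = 0.031. H0 is not rejected by the exact test, but would be if the critical value of 1 were kept.
- Both excluded without replacement: 0 in 18, p = 0.0056, H0 rejected.

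**The case against.** Several objections carry weight.

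- **Share unknown.** Treatment lasts about three weeks (15 fractions at 5 per week), while the endpoint window is 6 months. An event after the last fraction cannot cause early stopping, and a patient who pauses and then finishes has still received full therapy. The excluded share may be small. This stands, and it limits the size of the problem.
- **Inflation not assured.** With the exact critical value and modest exclusion, the level hardly moves. If event-free patients are lost too, it can fall below nominal, and lost power is then the likelier harm. This also stands. The larger figures in columns (b) and (c) need replacement of patients or an unadjusted critical value, and the article mentions neither.
- **Other reporting.** The adverse event tabulation and the promised emphasis on limitations would make excluded events visible. They do not change the hypothesis test.
- **Reading of the sentence.** The sponsor may have meant the ITT set. The sentence would then still need correcting, because it does not name that set.

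A reader might go further and infer that tumour control and survival will be overestimated. The documents do not support that. Those analyses are descriptive and use Kaplan–Meier and cumulative incidence methods. Death or relapse is an observed event, not missing documentation, and complete documentation is not defined as full 5-year follow-up. Nor does the eligibility condition in the ITT definition support the mechanism here, since it concerns baseline criteria and is not driven by toxicity.

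**Conclusion.** The choice of population is wrong for this endpoint as written. The direction is clear: exclusion linked to toxicity can only lower the tested rate. The size is not, and it would be too strong to say that the reported rate will be biased by a known amount.

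On assumed shares of 10 to 50% of event patients, with no event-free patient lost, the exact test's false-rejection probability runs from 0.025 to 0.079. It is up to 0.199 with replacement and up to 0.267 with an unadjusted critical value. If event-free patients are lost too, the cost may be power instead, because 20 patients leave no margin. In either case one or two patients can decide the conclusion. The correction should be made before the analysis, since it is cheap and the plan contains no other safeguard for the test.

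**What to change.** In section 2.4, and in the full protocol and SAP:

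- Name the primary set for the primary endpoint explicitly as all patients who received at least one fraction.
- Count every observed grade ≥ 3 skin event within 6 months that meets the endpoint definition, whether or not therapy or documentation was completed.
- State how treated, event-free patients without a full 6-month assessment are handled. One option is a primary analysis on patients who had an event or were assessed to 6 months, plus a sensitivity analysis counting the others as events. The rule against imputation should be worded to allow that sensitivity analysis. Simply counting them as event-free would again lower the rate.
- State that the critical value is derived for the number actually analysed.
- Keep the complete case set as a sensitivity analysis.
- Use all treated patients, with censoring, for the descriptive time-to-event endpoints.

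The cost is a wording change, with no added visits. If all 20 treated patients are evaluable, n = 20, the critical value of 1, the level of 0.0243 and the power of 0.88 are unchanged. If fewer are evaluable, the power loss shown above remains. The reported toxicity rate may be less favourable.

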## 2. Materials and Methods

### 2.1. Study Design

The BREAST (Partial breast reirradiation for breast cancer recurrences after repeat breast-conserving surgery with proton beam therapy, NCT06954623, clinicaltrials, registration date 1 May 2025) trial will be conducted as a prospective, single-arm, phase II study including 20 patients with histologically confirmed recurrent (or new primary) ipsilateral invasive breast cancer or ductal carcinoma in situ after the prior RT of the ipsilateral breast and with an indication for partial-breast re-RT. The patient and tumor characteristics are reported in the inclusion criteria in Table 1. Further, the patient and tumor characteristics, such as the histological subtype, hormonal and Her2neu receptor statuses, Ki67 proliferation index, the presence of lymphangiosis, tumor size, resection margin, patient age, and comorbidities will be assessed and reported. The patients will receive partial-breast re-RT with proton beam therapy, delivered with active raster scanning, in 15 once-daily fractions up to a total dose of 40.05 Gy(RBE) (relative biological effectiveness). The recruitment of the patients will start in 2025. The recruitment of the patients is planned over a time period of 36 months. The overall duration of the trial is expected to be approximately 48 months. The inclusion and exclusion criteria are described in Table 1.

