No imputation of the primary endpoint will be conducted. Missing values will be reported descriptively. Limitations associated with this statistical procedure will be reported with emphasis. Analyses of secondary, explorative, and translational endpoints will be descriptive and will include the calculation of appropriate measures reporting the means, standard deviations, medians, 1st and 3rd quartiles, the minimums and maximums for continuous or absolute data, and the relative frequencies for categorical variables. Time-to-event endpoints will be visualized by means of Kaplan–Meier plots and cumulative incidence functions. QoL analyses will be performed according to the corresponding EORTC manual. The safety analysis will comprise a tabulation and summary of (serious) adverse events. All the analyses will be performed using validated software. No interim analysis is planned.

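### The primary analysis set keeps only patients who complete the course with complete documentation, so patients stopped by grade ≥3 skin toxicity drop out of the toxicity rate under test

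*Protocol article*

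**What the plan says.** Section 2.4 defines two sets. The ITT set holds enrolled, eligible, consented patients who "have been treated for at least 1 day". The complete case set is the part of the ITT set "who were able to receive the planned therapy in full and whose documentation is correspondingly complete". The next sentence reads: "This is the primary evaluation population for primary and secondary endpoints". It follows directly on the complete case definition, so it makes that set primary. The article assigns no analysis to the ITT set.

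The primary endpoint is grade ≥3 acute or subacute skin toxicity, "assessed within the first 6 months after the start of the re-RT" (also section 2.2.1). The clock starts with treatment, so a reaction during the course is a primary event. On missing data, section 2.4 says: "No imputation of the primary endpoint will be conducted". It adds that limitations will be reported and that adverse events will be tabulated.

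**The concern.** Membership of the primary set depends on finishing all 15 fractions and on complete documentation. Grade ≥3 skin toxicity is a plausible reason for not finishing. A patient with a recorded event who then misses later visits may also fail the documentation condition. In both cases the event was seen, yet the patient is removed from the rate. This is selection on the outcome being tested. It differs from an eligibility exclusion and from simply having fewer than 20 evaluable patients. Replacing dropped patients until 20 completers are reached would hide the problem and not cure it.

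The null hypothesis is a rate of 25% or more, so removing event patients favours rejection. The decision turns on one event versus two, so one or two exclusions can decide the trial. The result is a safety claim intended to support a later randomized trial.

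**Working it through.** **Inputs (section 2.4).** n = 20; null rate 25%; assumed rate 3%; one-sided exact binomial test at 0.025; rejection only with at most 1 event; stated level 0.0243 and power 0.88. **Assumption:** q, the share of patients with an event who are dropped from the primary set. The article gives no value, so 10% to 50% is shown.

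**The plan's own figures.**
- Level: P(X ≤ 1 | 20, 0.25) = 0.75^20 + 20 × 0.25 × 0.75^19 = 0.0032 + 0.0211 = 0.0243.
- Power: P(X ≤ 1 | 20, 0.03) = 0.97^20 + 20 × 0.03 × 0.97^19 = 0.880.

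Both agree with the article.

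**Worked case (q = 100%, an illustration and not a forecast).** 20 patients are treated; 2 have grade ≥3 skin toxicity and both stop early.

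| Set | Events / n | Exact one-sided p against 25% | Upper 97.5% bound | Reject? |
|---|---|---|---|---|
| All treated | 2/20 | 0.091 | 31.7% | No |
| Complete case | 0/18 | 0.75^18 = 0.0056 | 1 − 0.025^(1/18) = 18.5% | Yes |

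With 3 such patients the comparison is 3/20, p = 0.225, against 0/17, p = 0.0075.

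**False-positive probability when the true rate among treated patients is p = 25%.** Three readings are shown, because the article states no replacement rule.

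- A: enrolment continues to 20 completers, rule of at most 1 event. The rate among those kept is p(1 − q)/(1 − pq) = 0.231 / 0.211 / 0.189 / 0.143 for q = 10 / 20 / 30 / 50%. The level is P(X ≤ 1 | 20, that rate).
- B: 20 treated, no replacement, rule of at most 1 event kept. Counted events are Binomial(20, p(1 − q)), with p(1 − q) = 0.225 / 0.200 / 0.175 / 0.125.
- C: 20 treated, no replacement, critical value recomputed at 0.025 for the number left. The number dropped is Binomial(20, pq), and the exact rejection probability is averaged over it.

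| q | A | B | C |
|---|---|---|---|
| 0 | 0.0243 | 0.0243 | 0.0243 |
| 10% | 0.0368 | 0.0416 | 0.0251 |
| 20% | 0.0560 | 0.0692 | 0.0284 |
| 30% | 0.0855 | 0.1118 | 0.0361 |
| 50% | 0.1986 | 0.2669 | 0.0795 |

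C is smaller because losing one patient makes the test stricter. At n = 19, at most 1 event has level 0.0310, so the critical value falls to 0 (level 0.0042). That costs power: at a true rate of 3% it drops from 0.880 to 0.561.

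**The case against.** The strongest reply concerns size. The critical value of 1 belongs to n = 20. If the exact test is applied to the patients actually analysed (series C), the level is 0.0251 at q = 10% and 0.0284 at q = 20%, barely above 0.025. Series B mixes the selection with a critical value that no longer fits, and series A assumes replacement, which the article does not mention. The course is about 3 weeks (15 fractions at 5 per week, section 2.3) within a 6-month window. Events after the last fraction, or after a pause followed by completion, therefore pass the treatment condition. The documentation condition might also mean only records of therapy or of the endpoint, not every later visit. Finally, excluded events would still appear in the adverse event tables.

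Much of this stands as a limit on magnitude: q is unknown, and the worked case is the extreme. It does not remove the flaw. The level exceeds 0.0243 in all three series at every q shown, and always in the direction of claiming safety. The safety tables and the promise to report limitations leave the tested rate unchanged. The ban on imputation is beside the point for events that were observed. Reading the sentence on the primary population as referring to the ITT set is grammatically possible but strained; if that was meant, the sentence still needs correcting. Nor can the choice be left to an SAP, since the article has already made it.

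**Conclusion.** The concern holds and must be fixed. As written, the primary analysis can discard an observed primary event because of the toxicity itself, and no exception prevents this. The direction of the bias is certain. Its size depends on how many event patients stop early or have incomplete records, which the article does not give. Over an assumed 10% to 50%, the level is 0.037 to 0.199 with 20 completers, 0.042 to 0.267 without replacement under the rule of at most 1 event, and 0.025 to 0.080 with the critical value recomputed. In the extreme case where both of two event patients stop, the conclusion reverses.

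**What to change.** In section 2.4 of the protocol, and in the SAP:

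- Make the primary set all patients who received at least one fraction of study re-RT. This also drops the eligibility condition in the present ITT definition, so say so explicitly.
- State that any grade ≥3 skin event observed within 6 months of the start of re-RT counts, whether or not the course was finished or later documentation is complete.
- Keep the complete case set as a sensitivity analysis only.

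Testing all 20 treated patients restores the stated level of 0.0243 and power of 0.880. How to treat patients lost before 6 months without an event is a separate question.

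The cost is wording only, with no extra patients or data. The downside for the sponsor is that the observed toxicity rate may be less favourable.

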#### 2.2.2. Secondary Objectives

The treatment response and progression will be defined based on clinical and radiological features, according to the most recent RECIST criteria (RECIST 1.1, Response Evaluation Criteria in Solid Tumors), with the evaluation of local, regional, and distant tumor control, as well as progression-free and overall survival at 1, 2, and 5 years after re-RT. Further, the toxicity (according to the CTCAE criteria) and the quality of life (with the EORTC QLQ-C30 and the supplementary questionnaire module QLQ-BR42 measuring specific quality of life aspects related to breast cancer treatment) will be assessed at baseline and during follow-ups for up to 5 years.

The cosmesis evaluation will include digitizer measurements (BRA, breast retraction assessment using the method by Vrieling et al. [50]) to quantitate the amount of retraction of the treated compared to the untreated breast. Two frontal views of the chest (from the neck to the midabdomen) will be taken, one with hands near the body and the other with the hands raised as far as possible above the head. A profile view of the treated breast (with the arms above the head) is also planned for each assessment. The suprasternal notch, as well as a point 25 cm below in the midline, will be marked (Figure 2).

A quantitative analysis will also be performed by a panel of doctors according to the graphic below. The three components of the indices (breast retraction assessment (BRA), percentage BRA (pBRA), and reference length (Ref)) will be determined as shown below and the resulting values will be calculated:(1)$$BRA=\sqrt{(a_{1}-b_{1}{)}^{2}+(a_{2}-b_{2}{)}^{2}}$$(2)Re⁡f=b12+b22(3)pBRA=BRARef×100

As this digitizer measurement method is reported to potentially miss some possible factors for poor cosmesis outcomes (e.g., if cosmetic changes were mainly due to skin alterations) and is weaker for inferiorly located tumors, another clinical rating system will be applied that assesses the overall subjective satisfaction of the patient and treating doctor in 4 categories: excellent/good/fair/poor overall cosmesis with the assessment of the surgical scar, breast size and shape, nipple position, and the shape of the areola by comparing the treated with the untreated breast.

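### Complete cases are the primary population for secondary CTCAE toxicity, so treated patients can leave the toxicity denominator

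*Protocol article*

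**What the plan says.** Section 2.4 of the protocol article defines two populations.

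- The ITT population consists of eligible, consenting patients who "have been treated for at least 1 day".
- The complete case population consists of ITT patients "who were able to receive the planned therapy in full and whose documentation is correspondingly complete".

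The next sentence is "This is the primary evaluation population for primary and secondary endpoints". It follows directly on the complete case definition and is in the singular, so the natural reading is that it refers to the complete cases.

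Section 2.2.2 lists among the secondary objectives: "Further, the toxicity (according to the CTCAE criteria) and the quality of life", which "will be assessed at baseline and during follow-ups for up to 5 years".

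Section 2.4 also plans a safety summary: "The safety analysis will comprise a tabulation and summary of (serious) adverse events". It does not say which patients that summary covers.

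**The concern.** A toxicity rate should count everyone exposed to the treatment. Membership of the complete case population is decided after exposure, by whether the patient finished therapy and whether the records are complete. Acute toxicity can interrupt a 15-fraction course, and a patient doing badly may also be harder to document. If patients with toxicity are lost from the denominator more often than patients without it, the rate among complete cases is lower than the rate among all treated patients.

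This matters because section 2.2 gives the analysis of toxicity as the specific purpose of the trial, and the Discussion says the study will supply the underlying data for a randomized trial. Section 1.2 shows that severe toxicity is a real prospect in this setting: the institution's own 25-patient re-RT series had late grade 3 toxicity in 12%. With 20 patients, one exclusion visibly moves the estimate.

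**Working it through.** **The plan's own figures.** The article gives no expected rate for secondary toxicity, so there is nothing to reproduce on that endpoint. The design figures for the primary endpoint do reproduce. With n = 20 and critical value 1:

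- P(X ≤ 1 | p = 0.25) = 0.0243, the stated level.
- P(X ≤ 1 | p = 0.03) = 0.880, the stated power.

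The planned number of treated patients, 20, is used below.

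**Step 1: which patients are counted.**

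| Patient | ITT | Complete case |
|---|---|---|
| Treated, full course, records complete | yes | yes |
| Treated, course stopped early | yes | no |
| Treated, full course, records incomplete | yes | no |

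The patients in the last two rows are exposed but not in the primary toxicity denominator.

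**Step 2: count example (assumed counts).** Exact (Clopper-Pearson) 95% intervals:

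- 2 events in 20 treated patients: 2/20 = 10.0% (1.2 to 31.7).
- One affected patient is not a complete case: 1/19 = 5.3% (0.1 to 26.0).
- Both affected patients are not complete cases: 0/18 = 0% (0 to 18.5).

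**Step 3: expected rate among complete cases.** Let p be the true rate in treated patients, q1 the proportion of patients with an event who are not complete cases, and q0 the same proportion among patients without an event. Then

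rate among complete cases = p(1 − q1) / [p(1 − q1) + (1 − p)(1 − q0)].

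Take p = 12%, the institutional late grade 3 figure in section 1.2. The values of q0 and q1 are assumptions; the article gives none.

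| q0 | q1 | Calculation | Result |
|---|---|---|---|
| 5% | 5% | 0.114 / (0.114 + 0.836) | 12.0% |
| 5% | 25% | 0.090 / (0.090 + 0.836) | 9.7% |
| 5% | 50% | 0.060 / (0.060 + 0.836) | 6.7% |
| 10% | 5% | 0.114 / (0.114 + 0.792) | 12.6% |

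Equal non-completion gives no bias. More non-completion among affected patients lowers the rate, and more among unaffected patients raises it slightly. With all treated patients in the denominator and their events counted, the expected rate is 12% throughout.

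**The case against.** **The pronoun is ambiguous.** The sentence naming the primary population could be meant for ITT. That is possible but is not the natural reading. If ITT was meant, one word corrects it.

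**Complete documentation may refer only to the therapy.** The definition sets no length of follow-up. If it demanded records out to 5 years, nobody could qualify within the stated trial duration of about 48 months, so that strict reading is unlikely. This stands in part. Late toxicity cannot stop a course that is already finished, so the link between late events and exclusion through documentation is uncertain. The other route remains: a patient who stops early because of acute toxicity leaves the primary denominator for all secondary toxicity, including later events.

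**The safety analysis may cover everyone.** It may. No restriction to complete cases is stated for it, and making one population primary does not forbid an ITT analysis. Section 2.4 also promises to describe missing values and stress limitations. But an adverse event table with no named population does not override an explicit rule for secondary endpoints, and reporting limitations does not put patients back in the denominator.

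**The size is assumed.** This is correct. The non-completion rates have no source in the article. The 12% comes from a mixed-technique series that included chest wall and nodal targets. Where Table 3 separates late grade 3 skin toxicity after proton re-RT, it is about 3 to 4%, under one patient in 20. The intervals for 2/20 and 1/19 overlap widely.

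**Stronger readings.** A reader might infer that reported toxicity will be too low. The article does not support that, because the bias can be zero or reversed. A reader might also infer that late grade ≥3 toxicity has been wrongly left without a landmark time or a cumulative incidence analysis, since 1, 2 and 5 years are given for tumor control, progression-free survival and overall survival. That does not follow either. Late grade ≥3 toxicity is not a named endpoint. The article nowhere says toxicity will be one pooled percentage. The plan that "Time-to-event endpoints will be visualized by means of Kaplan–Meier plots and cumulative incidence functions" lists no endpoints at all. Time points and estimators for a descriptive outcome are commonly left to the full protocol or analysis plan.

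**Conclusion.** The point holds for the analysis population. As written, the article makes complete cases primary for secondary CTCAE toxicity, so exposed patients can drop out of the denominator for reasons that may include toxicity. This is a stated rule, not a detail left for later. The result can understate harm; whether it does depends on who fails to complete.

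Under the assumed rates, a true 12% could appear as anything from 6.7% to 12.6%. In counts, one excluded patient with an event turns 10.0% into 5.3%. If nearly all patients finish the short course with full records, the effect will be negligible.

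The outcome is descriptive with no decision rule attached, so this is a modest point, worth correcting because the correction is cheap. The conclusion rests on the natural reading of the population sentence and is held with medium confidence.

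**What to change.** In section 2.4, add wording such as:

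> CTCAE toxicity endpoints and the safety analysis will use all patients who received at least one day of re-RT as the primary population. Results in the complete case population will be reported as a sensitivity analysis.

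The ITT population is close to what is needed, but it also requires patients to meet the eligibility criteria. The added wording should cover any treated patient, including one later found ineligible.

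The cost is two sentences and one additional descriptive presentation. CTCAE grades are already collected, so no new data are needed. There are two downsides: the reported toxicity rate may be slightly higher than among complete cases, and patients with partial follow-up must be handled explicitly, either as observed or as censored.
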